### Statistical analyses

**Primary Endpoint**

The number and proportion of patients with new T2 lesions at month 12 will be summarised by treatment group. A Fisher’s Exact Test (or chi-squared test, if required) will be conducted to test for the unadjusted influence of treatment group.

The primary comparison between the groups will be performed using a logistic regression analysis. In addition to a term for treatment, the following terms will be included in the logistic regression model: number of T2 lesions at baseline, number of Gd-enhancing lesions at baseline, relapse rate at baseline, baseline EDSS score, time since diagnosis, sex. The results will be presented as odds ratios, and associated 95% confidence intervals and p-values.

The number of T2 lesions at Month 12 will also be analysed, using analysis of covariance (ANCOVA). In addition to a term for treatment the following covariates will be included in the model: number of T2 lesions at baseline, number of Gd-enhancing lesions at baseline, relapse rate at baseline, baseline EDSS score, time since diagnosis, sex.

**Secondary Endpoints**

The change in the number of Gd-enhancing lesions on T1-weighted images detected from baseline to Month 12, the change in total T2 hyperintense lesion volume from baseline to Month 12, the change in total EDSS and total MSFC from baseline to Month 12, the change in functional sub-scores of EDSS and MSFC from baseline to Month 12, cortical atrophy from baseline to Month 12 and the change in concentration of sieric levels of antibodies (anti-MOG and anti-MBP) will each be analysed using an ANCOVA model which will include terms for treatment group, baseline value (relevant to each endpoint), number of T2 lesions at baseline, number of Gd-enhancing lesions at baseline, relapse rate at baseline, baseline EDSS score, time since diagnosis, sex. If any of the normality assumptions underlying the ANCOVA model cannot be substantiated then a non-parametric test (Kruskal-Wallis) will be used.

The proportion of patients in each treatment group who remain relapse free after 12 months will be analysed using a Fisher’s Exact test. While the time to first relapse will be summarised using a Kaplan-Meier plot with patients who do not experience a relapse by the Month 12 being regarded as censored observations at month 12. Patients who drop-out of the study prior to month 12 will be regarded as censored at the time of withdrawal.

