# Study Design

- Multi-center, rater-blinded, parallel-group, two arms, randomized study. Patients with relapsing-remitting forms of MS, **who have successfully finished the SWABIMS-Study**, respecting all inclusion/exclusion criteria, will be treated with the same medication they have received during the SWABIMS-Study for another 12 months directly after finishing the **SWABIMS-Study**.
- In the **SWABIMS-study**, 80 patients with relapsing-remitting MS were randomized to either an Interferon-beta-1b-monotherapy (subcutaneous every other day) **or** to a treatment with Interferon-beta-1b (subcutaneous every other day) plus Atorvastatin 40mg/d for 12 months after they were treated with Interferon-beta-1b (subcutaneous every other day) for 3 months.
- Enrolment of approx. 60 patients (one half in the Atorvastatin group) is planned.
- Patients providing written informed consent will be ***treated for 12 months***.

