# STATISTICAL METHODS

## Statistical evaluation

### Methods of statistical analysis

The methodology described in the protocol represents the methods foreseen at the time of writing, but advances in medical or statistical understanding may necessitate amendments to the approach, which will be documented in the statistical analysis plan. Full details of the methodology, including handling of missing or spurious data, will be described in the statistical analysis plan. No person privy to unblinded data will participate in discussions concerning changes in the statistical analysis plan.

All statistical hypothesis tests will be two-sided tests performed at the 5% significance level. All confidence intervals will be two-sided 95% confidence intervals unless stated otherwise.

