### MRI scan analysis

Two experienced observers will be in charge of lesion identification and counting. All scans from a given patient will be evaluated by the same observer. Doubtful cases will be assessed by the observers by consensual agreement. The readers were masked to clinical events or treatment.

A single enhancing lesion is defined as an area of enhancement seen on a given 3 mm axial image, which is referable neither to normally enhanced structures, nor to contrast migration within vessels. T2-weighted FSE/TSE images will be used as reference for analysis. A single T2 lesion is defined as an area of increased signal on a given 3 mm axial image, which should be seen on both T2- and proton density-weighted images and which is not referable to normally hyperintense structures. Lesions that changed during the study were categorized as new, enlarging, or recurrent. New T2 lesions are those which appear in areas where on the previous scan no abnormality was detected.

Lesion load will be assessed by trained technicians. The same technician will measure abnormalities on the scans from the same patients throughout the entire study. The image analysis will be performed using a semi-automated segmentation technique based on local thresholding.

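### The non-normality fallback for the secondary endpoints drops all covariate adjustment, and for the change in Gd-enhancing lesion number that fallback will probably be the analysis

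*Protocol*

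**What the plan says.** The Secondary Endpoints part of protocol Section 11.1.4 lists the outcomes to be analysed by ANCOVA. The first is "The change in the number of Gd-enhancing lesions on T1-weighted images detected from baseline to Month 12". T2 lesion volume, EDSS and MSFC totals and sub-scores, atrophy and the anti-MOG and anti-MBP antibodies follow. Each model contains treatment, the endpoint's own baseline value, and "number of T2 lesions at baseline, number of Gd-enhancing lesions at baseline, relapse rate at baseline, baseline EDSS score, time since diagnosis, sex". For the Gd endpoint the baseline value is already one of these six.

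The rule at issue comes next: "If any of the normality assumptions underlying the ANCOVA model cannot be substantiated then a non-parametric test (Kruskal-Wallis) will be used". It names no criterion for the normality check and no estimate to go with the rank test.

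Two other statements limit the point. Section 11.1.1 says "Full details of the methodology, including handling of missing or spurious data, will be described in the statistical analysis plan". The Primary Endpoint part of Section 11.1.4 has its own ANCOVA, for the total number of T2 lesions at Month 12 with the baseline T2 number as a covariate. No switch to a rank test is written there.

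**The concern.** The protocol chooses covariates for the secondary analyses and then gives them up whenever normality is doubtful. With two groups, Kruskal-Wallis is an unadjusted rank comparison: the baseline value stops being a covariate and the rest of the list goes with it. Lesion-count changes in patients on interferon are likely to include many zeros, so normality is very unlikely to be substantiated for Gd. The adjusted analysis that the protocol describes would then hardly ever be the one reported for that endpoint.

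At stake are power in a trial of about 60 patients and the content of the result. The rank test by itself gives a p-value but no size of effect.

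**Working it through.** **Inputs from the protocol.** Section 11.1.1: "All statistical hypothesis tests will be two-sided tests performed at the 5% significance level". Section 7: "Enrolment of approx. 60 patients (one half in the Atorvastatin group) is planned", so about 30 per arm. No lesion rate, SD, target effect or power is stated. There is therefore no figure to reproduce, and everything below rests on assumed ranges.

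**Step 1: subtracting baseline is not the same as adjusting for it.** Take a normal outcome with SD 1 and baseline correlation ρ. The effective SD is √(1−ρ²) for ANCOVA and √(2(1−ρ)) for an unadjusted change. The variance ratio of change to ANCOVA is 2(1−ρ)/(1−ρ²) = 2/(1+ρ). Power = Φ[(δ/SD)·√(n/2) − 1.96], with n = 30 and an assumed δ = 0.6.

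| ρ | Variance ratio 2/(1+ρ) | Power, ANCOVA | Power, unadjusted change |
|---|---|---|---|
| 0.3 | 1.54 | 0.68 | 0.50 |
| 0.5 | 1.33 | 0.77 | 0.64 |
| 0.7 | 1.18 | 0.90 | 0.85 |

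**Step 2: how often the fallback applies to Gd.** Simulated Gd counts were gamma-Poisson: patient i has activity fᵢ (gamma, mean 1, shape k), a baseline count Poisson(m·fᵢ) and a Month 12 count Poisson(m·fᵢ·RR) in the atorvastatin arm. Over assumed means m of 0.2 to 2, between 41% and 82% of changes are exactly zero. With m = 1, shape 0.5 or 0.25, and Shapiro-Wilk p < 0.05 on the residuals as an assumed trigger, the switch fires in 93-100% of trials.

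**Step 3: what the fallback costs.** In the m = 1 scenarios of Step 2, run both with fᵢ persisting between scans and with it drawn afresh, the protocol's ANCOVA has power 0.13-0.36 at RR 0.5 and 0.36-0.78 at RR 0.25. Kruskal-Wallis on the change has 0.08-0.26 and 0.19-0.51. So the switch moves from a stronger test to a weaker one.

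**Step 4: a rank test that keeps baseline.** This compares Kruskal-Wallis on the change with a rank ANCOVA of the Month 12 count on the baseline count (Quade), 30 per arm:

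| Scenario | Kruskal-Wallis | Rank ANCOVA |
|---|---|---|
| m 0.5, k 0.6, RR 0.5 | 17% | 22% |
| m 0.5, k 0.6, RR 0.35 | 24% | 39% |
| m 0.2-1, k 0.3-0.6, RR 0.5 | 9-26% | 11-33% |
| m 0.2-1, k 0.3-0.6, RR 0.35 | 12-41% | 18-57% |

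In the first two rows the gain is 22 − 17 = 5 and 39 − 24 = 15 percentage points. Type I error of the rank ANCOVA was 4.5-5.6%. That of the protocol's two-stage rule was 0.046-0.056.

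**Step 5: an assumption inside Step 4.** The arms were given equal rates at baseline. Under Sections 7.2.2 and 10.1, baseline is the last visit of the parent study, when Group 1 has already had 12 months of atorvastatin. If the drug has a steady effect present at both scans (m 0.5-1, k 0.6, RR 0.5 or 0.35), Kruskal-Wallis on the change rejects in only 4-6% of trials. The rank ANCOVA rejects in 11% (RR 0.5) and 18-20% (RR 0.35).

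**Step 6: where the gain disappears.** It shrinks or reverses at high lesion rates with strong heterogeneity, and when the outcome is very highly correlated with baseline. In a simulated T2-number change (baseline mean 25, new lesions mean 2.5), rank ANCOVA had 0.29 against 0.30 for Kruskal-Wallis at RR 0.5, and 0.69 against 0.78 at RR 0.25. The switch does not cover T2 number, but T2 volume, which it does cover, could behave similarly.

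**The case against.** The strongest reply is that these are secondary analyses, that the normality criterion and accompanying estimates are ordinary content for a statistical analysis plan that is not shown, and that a rank test is sometimes the better choice. Much of this stands. The missing criterion is not itself the fault, and nothing says that only a p-value will be reported. For heavy-tailed continuous changes (t with 2-3 degrees of freedom), Kruskal-Wallis had 0.50-0.66 power against 0.28-0.47 for ANCOVA. What the reply does not remove is that the protocol itself names the unadjusted test.

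A reader might infer more than the documents support:

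- **That baseline is ignored.** It is not. The rank test is applied to a change, so baseline is still subtracted; what is lost is its role as a covariate.
- **That the Month 12 T2 total is also exposed, or wrongly analysed.** The switch does not reach it. With baseline T2 number in the model, ANCOVA of the total gives the same treatment estimate as ANCOVA of the change, and is valid. Section 15.1.6 classifies new lesions separately ("Lesions that changed during the study were categorized as new, enlarging, or recurrent"), so a count analysis of new T2 lesions is possible, but it is an optional supportive addition.
- **That choosing the test from the data inflates false positives.** The simulated two-stage rule stays near 5%.
- **That Gd changes are known to be mostly zero.** No lesion rate is given. This is a likely pattern, not a documented one.
- **That a negative binomial model is the obvious replacement.** At m 0.5, k 0.6 and 30 per arm, one implementation failed to fit in 9-16% of trials and had type I error of 7-8%.

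**Conclusion.** The point holds for the fallback rule in the Secondary Endpoints part of Section 11.1.4, and chiefly for the change in Gd-enhancing lesion number. There the unadjusted rank test is likely to become the actual analysis, without the covariates that the protocol selected. The cost is moderate: about 5 to 15 percentage points of power in the central scenario (mean 0.5, shape 0.6), and less or none in the settings of Step 6. These sizes depend on assumed lesion rates, heterogeneity, rate ratios and, for the switch frequency, an assumed Shapiro-Wilk trigger. Power for Gd is low to moderate with either test at these rates, so the change improves a weak analysis without making it strong. Type I error and the primary logistic regression are not affected. The correction is worth making because it is specific and cheap.

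**What to change.** In the Secondary Endpoints part of Section 11.1.4:

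- **Gd lesion number:** prespecify a baseline-adjusted rank ANCOVA (Quade) as the analysis, not triggered by a normality check.
- **Other endpoints under the same sentence:** replace Kruskal-Wallis as the fallback with the same rank ANCOVA, so that baseline stays in.
- **Estimate:** Quade's test gives none either, so report a treatment effect with a 95% confidence interval beside it. Examples are the adjusted mean difference with a bootstrap interval, or a rate ratio with a permutation p-value.
- **Optional:** add a supportive count analysis of new T2 lesions.

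The cost is a change of wording and slightly more analysis work, with no new data. A little power is given up in the few settings named in Step 6.

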## Secondary endpoints

- Gd-enhancing lesion on T1-weighted images after 12 months of treatment
- Change of total T2 hyperintense lesion volume after 12 months of treatment (burden of disease, BOD)
- Clinical disease progression (EDSS, MSFC)
- Functional system scores (of EDSS and MSFC)
- Number of relapse-free patients after 12 months of treatment
- Relapse rate after 12 months of treatment
- Time to first relapse
- Cortical atrophy (changes in brain volume, changes in grey matter and white matter) after 12 months of treatment
- Sieric levels of antibodies against myelin oligodendrocyte glycoprotein (anti-MOG) and against myelin basic protein (anti-MBP)
- Sierial levels of neutralizing Antibodies (Nab)

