### Removal of patients from the study

- Every patient or his/her legal representative has the right to refuse further participation in the study at any time and without providing reasons. A patient's participation is to terminate immediately upon his/her request. The investigator should seek to obtain the reason.
- The patient may be withdrawn from the study at any time at the investigator’s discretion; the reason should be documented.
- Patients who withdraw from the study will not be replaced.
- There are two different types of patient **withdrawals** that may be decided:
  1. Withdrawal from further **study participation**; *i.e*. study treatment will be discontinued and no further data will be collected for the patient withdrawn. For this type of withdrawal, before withdrawal all efforts should be made to perform all assessments scheduled for the end-of-study visit (except MRI).
  2. Withdrawal from further **study medication** without termination of study participation.

If premature termination of study medication is decided for a patient, all efforts should be made to keep that patient on the original visit schedule until the regular end-of-study visit *(i.e.*, irrespective of study medication, each randomized patient should be followed up for the originally scheduled duration).

For both types of withdrawal, the following general rules apply: as far as possible, any withdrawal of a patient should be decided only after consultation with the sponsor.

The reasons for any withdrawal are to be fully documented on the case report form (CRF).

- **Withdrawal criteria**

A patient must be withdrawn from further **study participation** under the following circumstances:

1. Withdrawal of consent: every patient has the right to refuse further participation in the study at any time and without providing reasons.
2. Participation in any other clinical trial during the duration of this study.

A patient must be withdrawn from further **study medication** under the following circumstances:

1. Non-attendance of visits

Study medication must be withdrawn if a patient does not attend two consecutive scheduled visits without a major reason agreed on by the sponsor.

1. Unauthorized use of study drug.
2. Pregnancy
   Patients who have been withdrawn from study drug treatment because of pregnancy should not undergo MRI scans while pregnant.
3. Psychiatric conditions

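### Time to first relapse, a listed secondary endpoint, gets a Kaplan-Meier plot but no between-group comparison; the only relapse test named is a conservative Fisher test on the 12-month proportion

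*Protocol*

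**What the plan says.** The Synopsis and section 6.2 list the number of relapse-free patients and "Time to first relapse" as separate secondary endpoints. The list in section 8.1.2 of variables to be compared between the two groups includes the first but not the second.

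Section 11.1.4 treats them as follows:
- **Relapse-free proportion:** "The proportion of patients in each treatment group who remain relapse free after 12 months will be analysed using a" Fisher's exact test.
- **Time to first relapse:** "the time to first relapse will be summarised using a Kaplan-Meier plot". Patients without a relapse are censored at Month 12, and drop-outs at the time of withdrawal.

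The section names no log-rank test, regression model, hazard ratio or Kaplan-Meier estimate with a confidence interval. It names no analysis of relapse rate either, so Fisher's test is the only between-group relapse test in the protocol.

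Section 11.1.1 sets the error level: "All statistical hypothesis tests will be two-sided tests performed at the 5% significance level". It leaves missing-data handling to the statistical analysis plan, which is not at hand. On size, section 7 says "Enrolment of approx. 60 patients (one half in the Atorvastatin group) is planned". Under section 7.1.3, when a patient leaves study participation, "no further data will be collected for the patient withdrawn", and withdrawn patients are not replaced. Section 11.1.2 bases all efficacy analyses on every randomized patient who took at least one dose.

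**The concern.** Section 11.1.4 defines a complete censored data set for time to first relapse and then only draws it. A listed endpoint therefore yields no between-group result, and the whole relapse comparison rests on Fisher's test. In a study of this size that test has three limitations:
- It is conservative, because few distinct tables are possible.
- It treats a relapse in month 1 and one in month 11 alike.
- It needs a yes/no status for each patient. A patient who leaves participation before any relapse has none, so the follow-up that patient did contribute cannot enter as what it is.

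At stake is power on the relapse question, which could be gained without new data, and an interpretable estimate for an endpoint the protocol says it will study.

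**Working it through.** **Inputs from the protocol.** About 60 patients, half per arm, so n = 30 per arm (section 7); two-sided 5% level (section 11.1.1); 12 months of follow-up (section 7); censoring at withdrawal or Month 12 (section 11.1.4).

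**Inputs assumed.** The protocol gives no relapse-free proportion, effect size, drop-out rate or power, so there is no stated figure to reproduce. I take constant relapse and drop-out hazards, a 12-month relapse-free proportion of s = 55% versus 85%, and drop-out of d = 0 or 15% per arm, with a smaller effect shown afterwards.

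**Step 1: true size of Fisher's test.** Enumerate all 31 × 31 outcomes for two arms of 30. Add the binomial probabilities of those with p ≤ 0.05 when both arms share the same relapse-free proportion p.

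| p | 0.5 | 0.6 | 0.7 | 0.8 |
| --- | --- | --- | --- | --- |
| True size | 2.7% | 2.6% | 2.6% | 2.2% |

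About half the nominal 5% is used.

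**Step 2: no drop-out.** The same enumeration at 55% versus 85% gives Fisher power of 64.5%. The log-rank test on the same exponential times, by simulation, has 74% to 76% over repeated simulations, so about 75%. The gap is about 10 percentage points with no censoring before Month 12.

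**Step 3: 15% drop-out per arm.** With relapse hazard λ = −ln s and drop-out hazard δ = −ln(1 − d), per 12 months:
- probability of an observed relapse = λ/(λ + δ) × [1 − s(1 − d)]
- probability of completing relapse-free = s(1 − d)

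For s = 0.55: λ = 0.598, δ = 0.163 and s(1 − d) = 0.4675. Observed relapse = 0.786 × 0.5325 = 0.419.

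For s = 0.85: λ = δ = 0.163 and s(1 − d) = 0.7225. Observed relapse = 0.5 × 0.2775 = 0.139.

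The expected proportions under each way of giving drop-outs a status, with the resulting power, are:

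| Analysis | Relapse-free, arm 1 vs arm 2 | Power |
| --- | --- | --- |
| Fisher, drop-outs counted relapse-free | 58.1% vs 86.1% | about 59% |
| Fisher, drop-outs excluded | 52.8% vs 83.9% | about 63% |
| Fisher, drop-outs counted as relapsed | 46.8% vs 72.3% | about 42% |
| Log-rank, censored as in section 11.1.4 | assumed 55% vs 85% | about 70% |

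The excluded row is 0.4675/(0.4675 + 0.419) and 0.7225/(0.7225 + 0.139). Against the two better codings, the log-rank gain is 7 to 11 points.

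**Step 4: a smaller effect, 60% versus 80%.** Without drop-out, log-rank has 41% and Fisher 30%. With 20% drop-out per arm, log-rank has 36%, and Fisher 25% (counted relapse-free) or 29% (excluded). The gap is similar, but neither test is well powered.

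**The case against.** **Two endpoints, one tested.** Fisher's test is a conventional and valid choice for a binary endpoint at this size, and leaving time to first relapse off the comparison list in section 8.1.2 is consistent with a descriptive role. Part of this stands: Fisher's test is not an error. But sections 6.2 and 11.1.4 both treat time to first relapse as a secondary endpoint, and a plot alone gives no effect estimate. A log-rank test also adds one more correlated test, which is a reason to make Fisher's test supportive.

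**Drop-out coding.** A reader might infer that the Fisher result rests on an arbitrary classification of drop-outs and that this is the defect. The protocol does not support that: section 11.1.1 leaves missing-data handling to the statistical analysis plan. A patient who relapses before leaving also has a known status, so only relapse-free withdrawals are affected. The protocol tries to keep those few. Section 7.1.1 requires willingness to continue visits after stopping drug, section 7.1.3 keeps such patients on schedule, and entrants have already finished the parent study.

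**False positives.** A reader might also infer that Fisher's test could inflate the error rate. With 70% relapse-free in both arms, it rejects about 13% of the time if drop-outs count as relapsed and drop-out is 5% versus 25%. Neither condition is in the protocol. With 5% versus 10% drop-out and the same coding, the rate is about 3%.

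**Censoring is not the main driver.** This stands. The gap is about 10 points with no drop-out and no larger with drop-out when drop-outs are excluded from Fisher's test. It comes mostly from discreteness and unused event times.

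**Log-rank has its own assumptions.** This also stands. If, with no true effect at 60% relapse-free, 30% of impending relapsers in one arm left just before relapse, log-rank would reject about 12% of the time and Fisher in completers about 7%. With unequal drop-out the log-rank advantage can vanish: for 60% versus 80% with 25% drop-out in the lower arm and 5% in the higher, power is 39% for log-rank and 41% for Fisher in completers.

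**Conclusion.** The point holds as a minor one. Section 11.1.4 gives time to first relapse no between-group comparison although its censored data are fully defined, and rests the relapse comparison on a test that is valid but conservative at about 30 per arm (true size 2.2% to 2.7%).

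Under the assumed hazards and equal drop-out, a log-rank test gains roughly 7 to 11 percentage points of power over Fisher's better codings: about 75% against 65% without drop-out, and about 70% against 59% to 63% with 15% drop-out. These figures rest on assumed relapse and drop-out rates, proportional hazards and non-informative censoring. The statement that no comparison is named concerns the protocol only; the statistical analysis plan may add one.

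The protocol does not support a claim that Fisher's test is invalid here, or that a missing drop-out rule is a fault. No stated number is wrong, and the primary analysis is unaffected.

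**What to change.** In section 11.1.4:
- Compare time to first relapse between groups with a two-sided log-rank test at the 5% level, using the censoring rule already written.
- Report the Kaplan-Meier 12-month relapse-free probability per arm, with the difference and its 95% CI.
- Keep Fisher's test on the relapse-free proportion as supportive.

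Add time to first relapse to the list in section 8.1.2, so that it matches the Synopsis and section 6.2.

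The cost is about two sentences of analysis text and one list entry, with no new data. The downsides are that the log-rank test assumes non-informative censoring, is most sensitive to proportional hazards and gives no exact p-value.
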